7. ELIGIBILITY CRITERIA

7.1. Inclusion Criteria

Any patient scheduled for major abdominal surgery via laparotomy.

Age ≥ 18 years.

Patient has given informed consent in writing.

Patient is affiliated with a social security system (health insurance).

7.2. Exclusion Criteria

Exclusion criteria are:

Abdominal surgery via laparoscopy.

Contraindication to high lumbar/thoracic epidural placement (e.g., coagulation disorder, localized or systemic sepsis, shock or uncorrected hypovolemia, respiratory failure if block level above T7, severe aortic or mitral stenosis, obstructive cardiomyopathy, severe uncompensated heart failure, infection at puncture site).

Contraindication to IV lidocaine: allergy to local anesthetics, acute porphyria, unpaced atrioventricular conduction disorders, severe heart failure, severe liver failure, uncontrolled epilepsy, concomitant therapy with class I antiarrhythmic.

Contraindication to ropivacaine: allergy to local anesthetics, acute porphyria.

Failure to successfully place the epidural.

Major hepatectomy with vascular clamping.

Patient under 18 years of age.

Patient under legal protection (guardianship) or deprived of liberty.

Patient who is pregnant or breastfeeding.

Patient refusal to participate.

Patient not affiliated with a social security system.

7.3. Feasibility and Recruitment Methods

The possibility of participating in the protocol will be discussed during the Pre-Anesthesia Consultation (CPA), which is scheduled between 2 months and 48 hours before the planned surgery (on average about 3 weeks before surgery at CHU Amiens-Picardie). During this consultation, the protocol procedures will be explained to the patient. The informed consent will be obtained at the Pre-Anesthesia Visit (typically the day before surgery), to allow the patient time to consider their participation. Based on our current surgical caseload, we estimate that we can recruit the planned number of patients (50) within 12 months.

8. STUDY TREATMENTS/STRATEGIES/PROCEDURES

8.1. Investigational Treatment/Strategy/Procedure

Upon the patient’s arrival in the operating room, a thoracic epidural is placed by the anesthesiologist. This involves inserting the catheter into the epidural space, but initially no local anesthetic is injected through the epidural catheter. The conduct of general anesthesia—its induction and maintenance—is left to the discretion of the attending anesthesiologist in the operating room. At induction, lidocaine is administered intravenously at 1.5 mg/kg as a bolus, followed by a continuous IV infusion at 2 mg/kg/h until surgical closure, in accordance with SFAR guidelines. The use of intravenous lidocaine in this manner is consistent with its approved labeling. At surgical closure, the lidocaine infusion is stopped, and the epidural is activated with ropivacaine 1 mg/mL, given as an initial bolus of at least 5 mL and then continued at a minimum rate of 5 mg/h for 24 hours postoperatively. The use of ropivacaine in this manner is also in line with its approved labeling. As part of this study, blood samples will be taken to measure plasma lidocaine levels at: 30 minutes after the induction bolus, at the end of the continuous infusion, and 2 hours after the start of the epidural ropivacaine infusion. Blood samples to measure plasma ropivacaine levels will also be taken: 2 hours after the start of the epidural, and 24 hours after the start of the epidural. Each blood sample is 6 mL.

8.1.1. Study Drug Handling

8.1.1.1. Supply of Products

All medications used in the study are approved (have marketing authorization in France). Ropivacaine and lidocaine will be supplied by the hospital pharmacy of CHU Amiens-Picardie.

8.1.1.2. Product Packaging

The packaging will be the standard commercial packaging (as authorized by their marketing approvals) and will not be modified for the study.

8.1.1.3. Product Labeling

The labeling of the products will not be modified.

8.1.1.4. Dispensation of Products

Ropivacaine and lidocaine are routinely used and stored in the department by trained healthcare staff. They will be used in accordance with their approved indications. Staff will document their use in the patient’s medical record, noting the dose administered and the batch number used.

8.1.1.5. Storage

The drug units are stored in the clinical department under the conditions described in their Summary of Product Characteristics (SPC).

8.1.1.6. Return and Destruction of Unused Products

Used treatment units (e.g., empty vials or bags) are destroyed immediately after use by the clinical department via the usual biohazard waste disposal route. Any unused study drug (if applicable) will be disposed of similarly. There is no provision for returning unused study drugs to the pharmacy; they will be discarded per hospital protocol.

8.1.2. Blinding (Masking)

8.1.2.1. Organization of Blinding

Not applicable – this study is not blinded (open-label).

8.2. Associated Treatments and Procedures (if any)

Not applicable to this study

(Section numbering is maintained for structural consistency.)

9. ASSOCIATED TREATMENTS AND PROCEDURES

9.1. Allowed Associated Treatments/Procedures

Each patient will undergo general anesthesia conducted as per the usual care for this type of surgery. The choice of anesthetic protocol and any adjunct analgesic medications is left to the discretion of the anesthesiologist responsible for the patient on the day of surgery.

9.2. Prohibited Associated Treatments/Procedures

There are no prohibited procedures in this study; no specific co-interventions are disallowed beyond standard contraindications.

10. CONDUCT OF THE STUDY

10.1. Study Schedule

Start of inclusions: Immediately after obtaining the required regulatory approvals.

Inclusion period duration: 12 months.

Duration of participation for each patient: 48 hours.

Total study duration: 12 months.

10.2. Patient Follow-up Summary Table

The following table summarizes the timing of study-related procedures for each patient:

| Procedure / Assessment | Pre-inclusion (Day -60 to -2) | Inclusion (Day 0) | Visit 1 (30 min after lidocaine bolus) | Visit 2 (At surgical closure) | Visit 3 (2 h post-surgery) | Visit 4 (24 h post-surgery) | Visit 5 (Post-op Day 2) |
| --- | --- | --- | --- | --- | --- | --- | --- |
| Patient information | ✓ | ✓ |  |  |  |  |  |
| Informed consent |  | ✓ |  |  |  |  |  |
| Lidocaine level (lidocainemia) |  |  | ✓ | ✓ | ✓ |  |  |
| Ropivacaine level (ropivacainemia) |  |  |  |  | ✓ | ✓ |  |
| Adverse event monitoring |  |  | ✓ | ✓ | ✓ | ✓ | ✓ |

10.3. Pre-Inclusion Visit

The pre-inclusion visit is carried out by the investigator (study physician). It takes place between 2 months and up to 2 days before the inclusion visit, during the Pre-Anesthesia Consultation (CPA). All patients who are potential candidates (meeting inclusion criteria and no exclusion criteria) will be offered participation in the study. Information: During the pre-inclusion visit, the investigator informs the patient about the study and answers all questions regarding the study’s objective, the nature of the constraints, foreseeable risks, and expected benefits. The investigator also explains the patient’s rights in the context of research and verifies eligibility criteria. A copy of the information sheet and consent form is given to the patient at this time.

10.4. Randomization

There is no randomization in this study (it is a single-arm descriptive study).

10.5. Inclusion Visit

This takes place no later than the day before the surgery, conducted by the investigator. Consent acquisition: During the pre-inclusion visit (CPA), the investigator provided all the study information to the patient and answered questions about the study’s objectives, constraints, risks, and potential benefits, as well as explained the patient’s rights in a biomedical research context. The eligibility criteria were also verified. The patient was given the information sheet and consent form to review. After this information session, the patient is given time to consider their decision. The investigator is responsible for obtaining the patient’s written informed consent. The consent form must be signed before any study-specific clinical or paraclinical examination is performed.If the patient agrees to participate, both the patient and the investigator will print their names, date, and sign the consent form. The distribution of the information sheet and consent copies is as follows:

One signed copy of the information sheet and consent is given to the patient.

The original signed consent form is kept by the investigator (even if the patient moves or transfers care during the study) in a secure location inaccessible to third parties.

The patient’s medical history, clinical examination, and any usual care paraclinical exams (e.g., cardiology consult, TTE, ECG, liver function tests, gastroenterology consult, etc.) will be reviewed to ensure no contraindications to epidural or the use of the study anesthetics are present, both at the CPA and confirmed at the Pre-Anesthesia Visit (usually the day before surgery). Specifically, for the epidural: no coagulation disorders, no localized or systemic infection, no shock or uncorrected hypovolemia, no respiratory failure if high block, no severe aortic/mitral stenosis, no obstructive cardiomyopathy, no severe uncompensated heart failure. For lidocaine: ensure no allergy to local anesthetics, no acute porphyria, no unpaced AV block, no severe heart failure, no severe liver failure, no uncontrolled epilepsy. For ropivacaine: ensure no allergy to local anesthetics or acute porphyria.

10.6. Follow-up Visits

Follow-up begins once anesthesia induction is done and the lidocaine bolus has been administered. Clinically, this involves continuously monitoring and checking for any occurrence of local anesthetic adverse effects (cardiac and/or neurotoxicity) via physical exam and patient monitors (continuous ECG, BIS, invasive or non-invasive blood pressure, etc.) throughout the surgery and up to 24 hours postoperatively, whether the patient is in a standard ward or in ICU. We will also perform plasma measurements of lidocaine and ropivacaine at specific perioperative times: three lidocaine levels in total – the first 30 minutes after the induction bolus, one at the time the infusion is stopped (surgical closure), and the last one 2 hours after the epidural ropivacaine bolus; and two ropivacaine levels – the first 2 hours after the epidural bolus (at the same time as the last lidocaine level) and the second at 24 hours after epidural initiation.

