
3.2. Research Hypotheses and Expected Results

Our hypothesis is that combining continuous IV lidocaine infusion with epidural anesthesia during management of a major abdominal surgery does not increase the plasma concentrations of local anesthetics beyond toxic thresholds. Through repeated blood sampling, we hope to show that plasma levels of the local anesthetics remain well below toxic values. Furthermore, by observing an absence of adverse events related to local anesthetic use (central nervous system effects – which are rare – such as seizures, dizziness, loss of consciousness, paresthesia, tongue numbness, hyperacusis, tinnitus, visual disturbances, dysarthria, muscle tremors; hypoesthesia; and cardiac effects such as bradycardia, tachycardia, conduction disturbances up to cardiac arrest), we hope to demonstrate no cumulative cardiac or neurological toxicity when both are used together.

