5.2. Secondary Endpoints

The secondary endpoint is the occurrence (yes/no) of adverse events related to the use of local anesthetics, defined as any of the following:

Central nervous system symptoms: seizures, dizziness, loss of consciousness (“attacks”), paresthesia, numbness of the tongue, hyperacusis, tinnitus, visual disturbances, dysarthria, muscle contractions, tremors. Cardiac symptoms: bradycardia, tachycardia, conduction disorder possibly progressing to cardiac arrest. (If at least one of the above events occurs, it will count toward the endpoint.)

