12.2. Statistical Methods

Quantitative variables will be described as mean ± standard deviation and median [range]. Qualitative variables will be described as percentages with 95% confidence intervals

Primary endpoint analysis: We will calculate the percentage of patients who have at least one plasma concentration of ropivacaine or lidocaine outside the safe range. A 95% confidence interval (using an asymptotic or exact method as appropriate) will be computed for this percentage.

Secondary endpoint analysis: The percentage of patients experiencing a toxic event will be calculated with a 95% confidence interval (asymptotic or exact method). All statistical analysis will be performed using SAS software version 9.4

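### Eight of the eleven CNS items in the clinical toxicity endpoint cannot be elicited under general anaesthesia, and the protocol does not say from when they count

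*Protocol*

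**What the plan says.** **Endpoint.** Protocol Section 5.2: "The secondary endpoint is the occurrence (yes/no) of adverse events related to the use of local anesthetics". The CNS list begins "seizures, dizziness, loss of consciousness (“attacks”), paresthesia, numbness of the tongue, hyperacusis, tinnitus, visual disturbances, dysarthria" and ends with muscle contractions and tremors. The counting rule is "If at least one of the above events occurs, it will count toward the endpoint". Section 5.2 gives no time window and no category for an item that could not be assessed.

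**Setting.** Section 9.1: "Each patient will undergo general anesthesia conducted as per the usual care for this type of surgery". Lidocaine starts at induction (Section 8.1). It stops, and epidural ropivacaine starts, about 30 minutes before the end of surgery (Section 6.1).

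**Detection.** Section 10.6 starts follow-up after induction and the bolus. It provides for "continuously monitoring and checking for any occurrence of local anesthetic adverse effects (cardiac and/or neurotoxicity) via physical exam and patient monitors" (ECG, BIS and blood pressure are named) during surgery and to 24 hours afterwards. The Section 10.2 table ticks adverse-event monitoring at Visit 1 (30 minutes after the bolus), Visit 2 (surgical closure) and Visits 3 to 5 after surgery.

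**Analysis and inference.** Section 12.2: "The percentage of patients experiencing a toxic event will be calculated with a 95% confidence interval". Section 3.2 says that, from an absence of adverse events, "we hope to demonstrate no cumulative cardiac or neurological toxicity when both are used together".

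**The concern.** Most of the listed CNS events are things a patient reports or shows by responding. An anaesthetised patient can do neither, and ECG, BIS and blood pressure do not reveal tinnitus or tongue numbness. The protocol nevertheless schedules neurotoxicity checks in that period and draws one percentage from the whole of follow-up.

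An event confined to the anaesthetised period is therefore indistinguishable from no event. The error runs in one direction, towards the safety conclusion that the study hopes to reach. A reader of the final percentage would not know that, for most CNS items, the intraoperative period contributed no information.

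**Working it through.** **1. Which CNS items can be observed during surgery?** The classification of the Section 5.2 items is mine.

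| Needs an awake or responsive patient | Observable in principle |
|---|---|
| dizziness | seizures |
| loss of consciousness | muscle contractions |
| tongue numbness | tremors |
| paraesthesia | |
| tinnitus | |
| hyperacusis | |
| dysarthria | |
| visual disturbance | |

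That is 8 of 11. The list in Section 1 drops loss of consciousness and adds hypoesthesia, which also has to be reported, so the count there is again 8 of 11. The protocol does not say how far anaesthetic drugs mask the three motor signs.

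**2. Which window applies?**

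| Place | Window for clinical toxicity |
|---|---|
| Section 1, endpoints | within 48 hours after surgery |
| Section 5.2 | none stated |
| Section 10.2 | Visit 1 (during surgery) to postoperative Day 2 |
| Section 10.6 | from the bolus, through surgery, to 24 hours after |

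These do not agree on whether the operation counts.

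**3. What falls in the anaesthetised period?** The bolus, the whole infusion, two of the three lidocaine samples, and about the first 30 minutes after ropivacaine starts. Time to emergence comes on top and is not given.

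**4. How much lidocaine remains when symptoms can be reported?** Input: half-life T of 80 to 110 minutes (Section 3.3). Assuming first-order decay from the stop, the remaining fraction is 2^(−t/T).

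- t = 30 min (nominal end of surgery): 2^(−30/80) = 0.77; 2^(−30/110) = 0.83.
- t = 120 min (sample 2 hours after epidural start): 2^(−120/80) = 0.35; 2^(−120/110) = 0.47.

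So 77–83% remains at the nominal end of surgery and 35–47% at the 2-hour sample. These fractions describe residual exposure, not the share of events missed. They show that much of the overlap lies after surgery.

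**5. What could missed events do to the reported limit?** The protocol gives no precision figure for this endpoint. Its figures in Section 12.1 concern the primary endpoint with 50 patients: 1.96 × √(0.1 × 0.9/50) = 8.3% and 1.96 × √(0.5 × 0.5/50) = 13.9%, which match ±8% and ±14% to the whole point.

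For the clinical endpoint, suppose 0 of 50 patients have an event. The exact two-sided 95% upper limit is 1 − 0.025^(1/50) = 7.1%. If only a share s of patients with a true event could be detected, the limit on the true rate is 7.1%/s, and the chance of seeing no event at a true rate of 10% is (1 − 0.1s)^50. The protocol gives no value for s, so the values below are assumptions.

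| s | Upper limit on true rate | Chance of 0 of 50 at a true rate of 10% |
|---|---|---|
| 100% | 7.1% | 0.5% |
| 75% | 9.5% | 2.0% |
| 50% | 14.2% | 7.7% |
| 25% | 28.4% | 28.2% |

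**The case against.** A reader might infer that the entire CNS half of the endpoint is unobservable when it matters, and that patients are declared free of neurotoxicity by default. The documents do not support that, for four reasons.

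- Seizures, muscle contractions and tremors can in principle be seen, and Section 10.6 names physical examination and BIS.
- The endpoint is one yes/no per patient, not one per visit. Monitoring continues at Visits 3, 4 and 5 and follow-up lasts 48 hours (Section 6.1). Only an event confined to anaesthesia is lost.
- Section 15.1 provides codes for values that are not applicable, not done or not known. The CRF is not shown, so a recorded *no* at Visits 1 and 2 is an inference.
- Section 3.2 concerns the two drugs together. Until the lidocaine stops no ropivacaine is given, so the infusion period is lidocaine alone. The blind part of the overlap is its first half hour plus emergence, when ropivacaine levels are still rising according to Section 3.3.

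It is also fair to say that the limitation comes with any study under general anaesthesia, that the primary endpoint measures lidocaine at both intraoperative times, and that detailed coding rules can sit in an analysis plan.

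All of this narrows the point but does not remove it. No rule links the Section 15.1 codes to this endpoint. The window is contradictory in the protocol itself. Section 10.6 treats neurotoxicity as checkable throughout surgery, and no analysis plan can recover symptoms that could not be elicited.

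**Conclusion.** The point holds in a limited form and should be corrected. For 8 of 11 CNS items, the scheduled intraoperative checks cannot yield information, the endpoint does not acknowledge this, and its window is inconsistent. An absence of events therefore cannot support the neurological conclusion of Section 3.2 for the lidocaine infusion or for roughly the first 30 minutes of overlap.

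The downward bias applies only to symptomatic events confined to the anaesthetised period. Its size is unknown: the table in step 5 shows sensitivity to an assumed detectable share, not an estimate. The protocol also gives no concentration profile, so calling the blind period the time of highest lidocaine would be an inference from the dosing sequence. Postoperative follow-up still covers much of the overlap, and the cardiac component and the plasma-level primary endpoint are unaffected.

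The conclusion rests on the item classification in step 1 and on every patient remaining anaesthetised until about the end of surgery.

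**What to change.** 1. Reconcile the endpoint window across Sections 1, 5.2, 10.2 and 10.6, and state whether the intraoperative period counts.
2. In Section 5.2, define the patient-reported CNS items as assessed from emergence. At Visits 1 and 2 code them not assessable, using the Section 15.1 codes, rather than *no*.
3. In Section 12.2, report intraoperative cardiac events and observed motor signs (seizures, muscle contractions, tremors) separately from the postoperative CNS component.
4. Ask the listed CNS symptoms in a fixed order when the 2-hour sample is drawn, and code not assessable if the patient is still sedated. Adverse-event monitoring is already ticked at that visit. Section 10.2 labels it from surgery and Section 10.6 from the epidural bolus, so tie the questions to the sample itself.
5. Limit the Section 3.2 conclusion to neurological symptoms after emergence.

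The cost is CRF coding, a wording amendment and a short set of questions at an existing contact, with no extra visit or sample. The downside is a narrower claim: patient-reported neurotoxicity during the operation can no longer be said to have been excluded.

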10.7. End-of-Study Visit

The end-of-study visit corresponds to the last follow-up visit (Visit 5), which is performed on postoperative Day 2.

10.8. Rules for Discontinuing the Study

10.8.1. Withdrawal of a Participant from the Study

Any participant is free to withdraw from the study at any time, for any reason, upon request, without prejudice to their subsequent care. In the event of withdrawal, the ongoing standard treatment will be continued exactly as for patients not in the study, as participation in this study does not alter the therapeutic management. The date of withdrawal and the reason (if provided) will be recorded in the case report form (CRF) by the investigator. Every effort will be made to adhere to the protocol’s procedures. However, the clinician in charge of the patient may deviate from the protocol at any time if deemed necessary, particularly in the event of serious adverse events. Any such decision and its justification must be documented in the CRF. In case of major protocol deviations (regarding regulatory aspects, eligibility criteria, primary endpoint collection, etc.), the participant’s data may be excluded from analysis.

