5. ENDPOINTS

5.1. Primary Endpoint

The primary endpoint is the plasma concentration of ropivacaine and lidocaine falling outside the safe range at the various time points of patient management. We will obtain five plasma measurements of lidocaine and ropivacaine at different times during surgery and up to 24 hours postoperatively: lidocaine level at 30 minutes after the bolus injection, lidocaine level at the end of its infusion (i.e. at surgical closure), lidocaine level at 2 hours after induction of the epidural, ropivacaine level at 2 hours after induction of the epidural, and ropivacaine level at 24 hours after induction of the epidural. The toxic thresholds of these two local anesthetics are known: for lidocaine, the safe plasma range is 1.4 to 6 µg/mL; neurotoxicity appears from 15 µg/mL and cardiotoxicity from 21 µg/mL. For ropivacaine, the usual maximum total venous concentration not to exceed is around 2.2 µg/mL. Any single measurement above the toxicity threshold will be considered an occurrence of toxicity.

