11.2. Description of Expected Serious Adverse Events

The expected serious adverse events in this context are those related to the practice of regional anesthesia and the use of IV lidocaine and epidural ropivacaine. These include systemic toxicity from local anesthetics, severe allergic reactions to local anesthetics, and infections at the epidural puncture site.

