12. STATISTICAL ASPECTS

12.1. Calculation of Study Size

We anticipate that the proportion of patients with ropivacaine or lidocaine concentrations outside the safe range will be low. Assuming this proportion is around 10%, enrolling 50 patients would allow us to estimate this percentage with a confidence interval whose width does not exceed 16% (i.e., ±8% precision).

In any scenario, the percentage can be estimated with a precision no worse than ±14% (the worst-case precision corresponds to a proportion near 50%).

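### The exclusion clause in section 10.8.1 can take patients with an established event out of both the primary and the clinical toxicity analyses

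*Protocol*

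**What the plan says.** Two statements in protocol section 10.8.1 matter here, and they are separate. The first concerns care: the treating clinician "may deviate from the protocol at any time if deemed necessary, particularly in the event of serious adverse events", and must document the decision and its reason in the CRF. The second concerns data: "In case of major protocol deviations (regarding regulatory aspects, eligibility criteria, primary endpoint collection, etc.), the participant’s data may be excluded from analysis".

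Section 11.2 describes the serious adverse events that are expected: "These include systemic toxicity from local anesthetics", along with severe allergic reactions and puncture-site infections.

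On counting events, section 5.1 says: "Any single measurement above the toxicity threshold will be considered an occurrence of toxicity". For the primary analysis section 12.2 says: "We will calculate the percentage of patients who have at least one plasma concentration of ropivacaine or lidocaine outside the safe range". For the secondary analysis it says: "The percentage of patients experiencing a toxic event will be calculated with a 95% confidence interval". Section 12.1 plans for 50 patients and a proportion of about 10% outside the safe range.

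**The concern.** The study exists to count patients with unsafe levels or clinical toxicity. An exclusion rule for such a study should not depend, directly or indirectly, on whether the patient had the outcome. This one can. It is optional, its list of reasons is open-ended, it names collection of the primary endpoint as a ground, and it does not say who decides, when, or with what knowledge of the results. The study is open-label (8.1.2.1) and has no independent monitoring board (13), so no other provision in the protocol supplies that safeguard.

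At stake is the credibility of a low percentage. The abstract gives the purpose as demonstrating that the combination is safe. Losing event patients moves the estimate in that direction, and with about five events expected, each one carries weight.

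**Working it through.** **Step 1. Can an event lead to exclusion under the text?**

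- Local anesthetic systemic toxicity is an expected serious adverse event (11.2).
- A serious adverse event is the leading reason given for departing from protocol (10.8.1, first statement).
- Three of the five primary measurements are timed from the start of the epidural: lidocaine at 2 h, ropivacaine at 2 h and ropivacaine at 24 h (5.1). If an event interrupts the planned sequence, some or all of these may be missing.
- Missing primary measurements can be classed as a major deviation in endpoint collection, and the data may then be excluded (10.8.1, second statement).
- One measurement above threshold suffices for toxicity (5.1), and one out-of-range level suffices for the primary percentage (12.2). Later missing samples cannot undo an event already observed, yet they can be the ground for removing the patient.
- The exclusion is from the analysis in general, so the secondary percentage, which needs no assay at all, is affected too.

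The path exists, but it is an inference through the endpoint-collection ground and the open list. It is not spelled out.

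**Step 2. The plan's own precision.** Inputs from 12.1: n = 50, p = 10%, with a worst case at p = 50%; 95% confidence from 12.2. The half-width is 1.96 × √(p(1−p)/n).

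- p = 10%: 1.96 × √(0.10 × 0.90 / 50) = 0.083, stated as ±8%.
- p = 50%: 1.96 × √(0.50 × 0.50 / 50) = 0.139, stated as ±14%.

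Both reproduce to the nearest whole percent.

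**Step 3. Effect of losing event patients.** Expected events at the planning rate: 0.10 × 50 = 5. If k event patients are excluded, the estimate becomes (5−k)/(50−k). The exact (Clopper-Pearson) 95% limits for x events in n patients are the 2.5% quantile of Beta(x, n−x+1) and the 97.5% quantile of Beta(x+1, n−x). The protocol gives no exclusion rate, so k is an assumption.

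| Event patients excluded (k) | Events / n | Estimate | Exact 95% CI |
| --- | --- | --- | --- |
| 0 | 5/50 | 10.0% | 3.3% to 21.8% |
| 1 | 4/49 | 8.2% | 2.3% to 19.6% |
| 2 | 3/48 | 6.3% | 1.3% to 17.2% |

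Each excluded event patient lowers the estimate by just under 2 points. Two exclusions lower the upper limit by 21.8 − 17.2 = 4.6 points.

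**The case against.** **Serious adverse events are not in the exclusion list.** A reader might infer from the paragraph that patients with a serious adverse event are expressly liable to exclusion, or that any departure in care is enough. Neither is supported. Serious adverse events appear only in the permission to deviate, and only major deviations can lead to exclusion. This stands and limits the point to what the rule can do, not what it directs.

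**The statistical analysis plan may define the analysis sets.** It may, and it is not shown. But the protocol is not silent here: it states a rule. An analysis plan could use that permission in full and still comply.

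**Missing samples.** It is tempting to add that a patient kept in with missing samples counts as in range by default. Section 12.2 does not say how incomplete patients are handled, and that can be left to the analysis plan. Nor do missing assays affect the secondary endpoint, which is clinical. This is no part of the point.

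**Direction of bias.** Exclusion for missed samples can also remove patients without events, which raises the rate: dropping five such patients gives 5/45 = 11.1%. This is correct. The net direction is not known in advance. What can be said is that exclusions prompted by toxicity all push the percentage down.

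**Size.** The 10% refers to levels outside the safe range. Section 5.1 puts that range for lidocaine at 1.4 to 6 µg/mL and neurotoxicity from 15 µg/mL. A level outside the range, including one below 1.4 µg/mL, need not involve a serious event or any deviation. A scenario in which all five event patients vanish therefore has no basis in the protocol. Nor can one say that exclusions would change the study's conclusion, since sections 12.1 and 12.2 plan an estimate with an interval and set no decision threshold.

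**Events are still reported.** Serious events go to the sponsor at once (11.3), and those deemed drug-related enter the annual safety report (11.5). They are not lost from the safety record, but they could be lost from the two percentages that the study will report.

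**Conclusion.** The point holds in this form: section 10.8.1 allows outcome-related exclusion, at discretion, from an open list and without a decision masked to results. It can remove patients with established events from both the primary and the clinical toxicity analyses. Whether that would happen, and how often, cannot be read from the protocol.

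At the planning rate, losing one event patient moves the estimate from 10.0% to 8.2%, and losing two moves it to 6.3%, with the upper limit falling from 21.8% to 17.2%. These figures assume five out-of-range patients among 50, one or two of them excluded, and no exclusions among the others. They apply to the primary percentage; the protocol gives no expected rate for the clinical endpoint. This is a stated rule that needs correcting, not a detail left for later, and it can be corrected cheaply before results are known.

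**What to change.** Replace the last sentence of section 10.8.1 with a rule to this effect:

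- Every validly consented patient who received study drug stays in the clinical toxicity analysis, and every such patient with at least one assay result stays in the primary analysis.
- An observed out-of-range level or toxicity event always counts, whatever later samples are missing.
- Exclusion is limited to absent or withdrawn consent, or an eligibility violation already present before treatment. It is decided without knowledge of levels or events, and each exclusion is reported with its reason.

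Add two sensitivity analyses to section 12.2: one restricted to patients with all five results, and one restricted to patients who received both drugs. The second is needed because the wider set may include patients given lidocaine but never epidural ropivacaine, who say little about the combination.

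The cost is about a paragraph of text across the two sections, two short extra analyses and a slightly more heterogeneous analysis set. No further patients or samples are needed, and clinical care is unchanged.
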